## Abstract

**Background:**

Major depressive disorders rank in the top ten causes of ill health in all but four countries worldwide and are the leading cause of years lived with disability in Europe (WHO). Recent research suggests that neurodegenerative pathology may contribute to the development of late-life depression (LLD) in a sub-group of patients and represent a target for prevention and early diagnosis. In parallel, electroconvulsive therapy (ECT), which is the most effective treatment for severe LLD, has been associated with significant brain structural changes. In both LLD and ECT hippocampal volume change plays a central role; however, the neurobiological mechanism underlying it and its relevance for clinical outcomes remain unresolved.

**Methods:**

This is a monocentric, clinical cohort study with a cross-sectional arm evaluating PET-MR imaging and behavioural measures in 64 patients with LLD compared to 64 healthy controls, and a longitudinal arm evaluating the same imaging and behavioural measures after 10 ECT sessions in 20 patients receiving ECT as part of their normal clinical management. Triple tracer PET-MRI data will be used to measure: hippocampal volume (high resolution MRI), synaptic density using [^11^C]UCB-J, which targets the Synaptic Vesicle Glycoprotein 2A receptor, tau pathology using [^18^F]MK-6240, and cerebral amyloid using [^18^F]-Flutemetamol, which targets beta-amyloid neuritic plaques in the brain. Additional MRI measures and ultrasound will assess cerebral vascular structure and brain connectivity. Formal clinical and neuropsychological assessments will be conducted alongside experience sampling and physiological monitoring to assess mood, stress, cognition and psychomotor function.

**Discussion:**

The main aim of the study is to identify the origin and consequences of hippocampal volume differences in LLD by investigating how biomarkers of pathological ageing contribute to medial temporal lobe pathology. Studying how synaptic density, tau, amyloid and vascular pathology relate to neuropsychological, psychomotor function, stress and ECT, will increase our pathophysiological understanding of the in vivo molecular, structural and functional alterations occurring in depression and what effect this has on clinical outcome. It may also lead to improvements in the differential diagnosis of depression and dementia yielding earlier, more optimal, cost-effective clinical management. Finally, it will improve our understanding of the neurobiological mechanism of ECT.

**Trial registration:**

ClinicalTrials.gov Identifier: NCT03849417, 21/2/2019.

**Supplementary Information:**

The online version contains supplementary material available at 10.1186/s12888-021-03063-y.

## Background

Gaining insight into the pathogenesis of Late Life Depression (LLD) is crucial for treatment and prevention. Besides genetic vulnerability, environmental factors, coping strategies, and medical comorbidities, brain ageing and its effect on neural circuits involved in emotion regulation and cognitive functioning contributes to the development of depressive symptoms later in life [1]. Ageing is associated with multiple deleterious and dynamic processes in the brain which occur in parallel at different scales. These include a global loss of neurons and synapses manifesting as grey matter atrophy, deterioration in white matter leading to impaired neural connectivity, increased vascular pathology which impairs brain metabolism and promotes inflammatory processes, and the accumulation of toxic proteins such as beta-amyloid and hyperphosphorylated-tau. The idea that pathological brain ageing constitutes an important pathway to LLD is largely based on evidence that LLD is associated with an increased risk of developing cognitive decline and dementia [2]. Complementary models exist to explain the relationship. The increased risk in early-onset depression has mainly been related to stress, whereby the physiological effects of stress accelerate brain ageing (e.g. grey matter loss) and increase vulnerability to cognitive decline [3]. Cognitive decline in late-onset depression is often seen as support for the “neuropsychiatric model” whereby depression is a prodromal symptom of a neurocognitive disorder. Although the neuropsychiatric and stress models propose distinct theories, there is increasing evidence that stress interacts with neurodegeneration and cerebrovascular disease, enhancing pathological brain ageing [4]. According to the original neuropsychiatric model, lower hippocampal volume in LLD is mainly caused by preclinical or prodromal Alzheimer’s disease given that in a significant proportion of patients, LLD precedes the onset of dementia, particularly Alzheimer’s disease (AD) [5]. Moreover, higher amyloid beta burden is associated with increasing anxious-depressive symptoms over time in cognitively normal older individuals [6]. However, recent evidence from amyloid positron emission tomography studies have challenged the idea that amyloid pathology is central to the neurobiology of LLD [7, 8].

Suspected non-amyloid pathology (SNAP) is a biomarker-based concept that applies to individuals with normal levels of amyloid-β in the brain, but in whom other biomarkers of neurodegeneration are present [9]. Tau protein is abundant in neurons and plays an important role in promoting microtubule assembly and stabilizing microtubule networks. Pathological hyperphosphorylation of tau renders it insoluble and leads to its aggregation in neuronal soma and as neurofibrillary tangles. Whilst tauopathy plays a central role in AD, medial temporal tau pathology is also considered as the most important constituent of SNAP [9]. Intriguingly, depressive symptoms have recently been related to tau accumulation [10]. Moreover, animal studies suggest that stress, an important depression risk factor, may be synaptotoxic through hyperphosphorylated tau accumulation in the synapse [11]. Following the development of the next generation tau tracer [^18^F]MK-6240 which targets tau associated with neurofibrillary tangles [12] and [^11^C]UCB-J, which targets the Synaptic Vesicle Glycoprotein 2A receptor to estimate synaptic density [13], it is now possible to investigate the relationships between SNAP, primary age related tauopathy (PART) [14] and stress in LLD.

One therapeutic intervention that has a profound effect on medial temporal lobe structure in LLD is electroconvulsive therapy (ECT). ECT is a safe, rapid-acting antidepressant therapy that has repeatedly been shown to induce a transient increase in hippocampal volume [15, 16]. However, the exact origin of these structural changes and their implications for the dramatic clinical improvement (and transient cognitive side-effects) associated with ECT remains unknown. Based on preclinical research, the leading hypothesis is that volumetric changes reflect changes in synaptic plasticity [17]. For example, repeated electroconvulsive seizures increase the total number of synapses in adult male rat hippocampus [18] and increased expression of the synaptic plasticity proteins neural cell adhesion molecule 1 (NCAM1) and the presynaptic protein synapsin 1 (SYN1) have been reported in hippocampus and prefrontal cortex [19]. The translation of these preclinical findings to patients being treated with ECT is critical for understanding its mechanism of action, yet prior to the availability of [^11^C]UCB-J it was not possible to measure synaptic density in humans in vivo.

## Methods: Design

### Study aims and objectives

This study aims to shed light on how non-amyloid pathology may contribute to LLD pathology, identify the origin of LLD associated medial temporal lobe atrophy, and relate PET-MR imaging biomarkers to therapeutic response to ECT. Additionally, it aims to investigate the link between stress and MTL pathology. In order to achieve these aims, a number of objectives and associated hypotheses are proposed.

### Primary objectives

#### Objective 1

To examine whether lower hippocampal volume in LLD is associated with decreased synaptic density. *Hypothesis: Hippocampal volume will be positively correlated with synaptic density* i.e. *a lower hippocampal volume will be associated with a lower accumulation of MTL [*^*11*^*C]UCB-J.*

#### Objective 2

To study the relationship between medial temporal synaptic density and tau accumulation in LLD. *Hypothesis: Hippocampal volume will be negatively correlated with tau accumulation* i.e. *a lower hippocampal volume will be associated with a higher accumulation of MTL [*^*18*^*F]MK-6240.*

#### Objective 3

To examine whether hippocampal volume increase following ECT is associated with increased synaptic density. *Hypothesis: Hippocampal volume increase following ECT will be positively correlated with synaptic density* i.e. *Higher hippocampal volume will be associated with higher binding of MTL [*^*11*^*C]UCB-J following ECT.*

### Secondary objectives

#### Objective 4

(a) To study the relationship between medial temporal tau accumulation and the presence of white matter pathology (including WML) in tracts that are connected with the hippocampus. *Hypothesis: White matter pathology, such as WML and microstructural deterioration in MTL associated fibre tracts will be positively correlated with tau accumulation.*

#### Objective 5

To investigate whether cardiovascular risk factors are associated with biomarkers of pathological brain ageing e.g. increased white matter lesions, atrophy, and tau accumulation, and can be used in multivariate models to predict clinical outcomes. *Hypothesis: pathological ageing and microvascular damage are associated with cardiovascular risk factors and predict worse clinical outcomes in LLD.*

#### Objective 6

To relate medial temporal pathology to stress by means of ecological momentary assessment (EMA) combined with wearable biometric data collection devices and fMRI based functional connectivity measures. Hypothesis: Lower hippocampal volume and disrupted MTL functional connectivity will be associated with higher reactivity to stress and negative affect measures derived from EMA and physiological monitoring.

### Study design

#### Study setting

The study will take place in an academic hospital in Belgium and will involve data collection at two sites: the University Hospitals Leuven and the Department of Geriatric Psychiatry at the University Psychiatric Center KU Leuven. The main sponsor of the study is the KU Leuven in Belgium.

## Methods: participants, interventions, and outcomes

### Participants

A consecutive series of 64 patients (see power analysis) with late-life depression will be recruited from the Department of Geriatric Psychiatry of the University Psychiatric Center KU Leuven, Belgium. We will also include 64 age- and gender-matched healthy comparison subjects who have no prior or current depressive illness or cognitive impairment, as determined by formal clinical (psychiatric and neurological) and neuropsychological assessment (details below). Exclusion criteria will the same as for the patient group. All participants will be genotyped to determine apolipoprotein ε (APOE) status and need to provide written informed consent prior to enrolment in the study in accordance with the Declaration of Helsinki. Selection criteria are outlined below.

*Inclusion criteria*
Age over 60 years oldDiagnosis of late-life depression according to DSM 5 (LLD group)No evidence of major neurological disorder

*Exclusion criteria*
A history of any major disease that may interfere with the investigations (especially liver and kidney disease, or uncontrolled diabetes) or cancer;Any history of a major neurological disorder, in particular Alzheimer’s disease, Parkinson’s disease, stroke or TBI;A history or evidence of psychiatric disease, as assessed by clinical interview (control group).A current user (including “recreational use”) of any illicit drugs, including cannabis, or a history of drug or alcohol abuse;Chronic use of medication that has central nervous system effects (e.g. strong painkillers such as opioids)Exposure to ionizing radiation (> 1 mSv) in other research studies within the last 12 months;Contra-indication for MRI scanning;Claustrophobia or intolerance to confinement during PET-MRI scanning procedures; not being able to lie still for 60 min inside the scanner;Inability to understand the study procedures;Unwillingness or inability to perform all of the study procedures, or being considered unsuitable in any way by the principal investigator;ECT within the last 3 months before enrolment

### Interventions

In a subgroup of patients selected according to the clinical need for ECT (estimated *n* = 20, based on experience with earlier studies, see power analysis), ECT will be administered twice a week with a constant-current brief-pulse device (Thymatron System IV, Somatics, IL, USA). Anaesthesia will be achieved with intravenous administration of etomidate (0.2 mg/kg) and succinylcholine (1 mg/kg). Motor and EEG seizure will be monitored to ensure adequate duration and quality. Subjects will all be treated with right unilateral (RUL) ECT with stimulus intensity 6 times the initial seizure threshold (ST), as determined by empirical dose titration at the first treatment, until remission (Montgomery-Åsberg Depression Rating Scale (MADRS) < 10 in two consecutive ratings with a week interval). Subjects who failed to respond to RUL ECT after the sixth treatment will be switched to bitemporal ECT (1.5xST) (Dutch Guidelines for ECT [20]). The clinical criteria/indications for ECT are determined by the treating psychiatrist and include acute suicidality with high risk of acting out suicidal thoughts, psychotic features, rapidly deteriorating physical status due to complications from the depression (e.g. poor oral intake), history of poor response to medications, history of good response to ECT, patient preference, when the risks of standard antidepressant treatment outweigh the risks of ECT, particularly in medically frail or elderly patients, and catatonia.

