### Outcomes

The primary outcome measures for the cross-sectional part of the study are **hippocampal volume**, the amount of cerebral hyperphosphorylated **tau** in neurofibrillary tangles, and **synaptic density** (SV2A glycoprotein) as determined by SUVR values derived from uptake of the PET tracers 18F-MK-6420 and 11C-UCB-J respectively. The primary outcome measures for the longitudinal part of the study are **change in hippocampal volume, tau and synaptic density following ECT** as determined by a baseline measurement prior to ECT and a second measurement after 10 ECT sessions. A fixed number of sessions was chosen to reduce bias due to differences in treatment duration whilst ensuring adequate clinical response within the study population. The relationship between the primary and other outcome measures and the study objectives are outlined in Table 1. This study will additionally generate numerous outcome variables that can be used to address secondary hypotheses relating, but not limited to, the objectives in this study.

**Table 1 Tab1:** Research questions and outcome data to be used to address the study objectives

Objective	Research Question	Experimental data	Variables
1	Hippocampal atrophy associated with SD?	**MRI: 3D T1** BRAVO & **3D T2** (morphometry & PET pre-processing) **PET:** ^**11**^**C-UCB-J PET** (SV2a: SD)	Hippocampal volume ^11^C-UCB-J SUVR
2	Tau associated with SD in hippocampus?	**MRI: 3D T1 BRAVO** & **3D T2** (as above) **PET:** ^**18**^**F-MK-6240** (tau)	Hippocampal volume ^18^F-MK-6240 SUVR
3	ECT-induced ΔGM in hippocampus associated with ΔSD?	**MRI: 3D T1 & 3D T2** (as above + post ECT) **PET:** ^**11**^**C-UCB-J PET** (SD)	Δ Hippocampal volume Δ^11^C-UCB-J
4	Tau associated with MTL WM damage?	**MRI: 3D FLAIR** (to define + quantify WML) **SWI & ASL** (perfusion/vascular pathology) **multi-shell diffusion** (DKI, NODDI + tractography) **PET:** ^**18**^**F-MK-6240** (tau)	Total + regional cerebral WML volume ^18^F-MK-6240 SUVR WM microstructural damage (e.g. MK, FA, ND), MTL WM fibre bundles

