### Sample size

Our proposed sample size of 128 participants is based on the following calculations. As our hypotheses assume baseline group differences between controls and patients in hippocampal volume and synaptic density, and increases in hippocampal volume following ECT, we have based our power calculations on t-tests to determine such differences, rather than on correlations.

(1) Based on the results of our previous study [7] (Group 1 mean = 6396.251 mm^3^, Group 2 Mean = 6724.461 mm^3^, Group 1 Standard Deviation = 711.49 mm^3^ Group 2 Standard Deviation = 763.866 mm^3^), using the STATA statistical package POWER procedure, to have a power of at least 0.80 (0.804) to detect a group mean difference in normalized total hippocampal volume using a two-sample t-test with α-level of 0.05 (one-tailed), assuming a balanced design with equal group sizes, requires 64 subjects per group, i.e. 128 subjects in total.

(2) To examine hippocampal volume changes after ECT treatment we will assess normalized total hippocampal volume on a random sample of patients before and after the last ECT treatment. Based on the expected mean difference in normalized total hippocampal volume (− 188.333 mm^3^), pre 792.5462 mm^3^ and post standard deviations 864.075 mm^3^, and the correlation between pre and post volume hippocampal measurements (0.92908) from our previous study [15], to achieve 80% power (0.814) at an α-level of 0.05 (one-tailed) requires 20 subjects.

(3) Based on the results of a recent study [21] investigating differences in ^11^C-UCB-J binding in older healthy controls and AD patients with mild cognitive impairment and mild dementia (mean age = 73 years), (Group 1 mean = 0.87, Group 2 Mean = 1.47, Group 1 Standard Deviation = 0.5 Group 2 Standard Deviation = 0.37), to have a power of at least 0.80 (0.826) to detect a group mean difference in ^11^C-UCB-J (synaptic density) using a two-sample t-test with α-level of 0.05 (one-tailed), assuming a balanced design with equal group sizes, requires 8 subjects per group, i.e. 16 subjects in total.

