### Statistical analysis

The following section describes the specific analysis of imaging data as this will be used to derive the primary outcome measures hippocampal volume, synaptic density and cerebral tau burden. Note that in addition to these analyses, conventional statistical tests (e.g. t-tests, correlations, regression, and their longitudinal equivalents, paired-T, linear mixed models with repeated measures) will be applied to address the research questions outlined in objectives 1–6 and in Table 1 in accordance with how the data align with statistical assumptions (e.g. normality, homogeneity etc.).

In this prospective longitudinal study, we will first analyse individual modalities and sequences independently in univariate analyses to address the different modality and underlying physiological/morphological research questions. More specifically, to investigate whether hippocampal volume is associated with tau and synaptic density we will perform voxel-wise linear regression analysis in SPM12, including age and total intracranial volume as covariates. To investigate whether hippocampal volume change following ECT is associated with a corresponding change in synaptic density we will apply a longitudinal linear mixed model controlling for age, in which hippocampal volume and hippocampal synaptic density are dependent variables.

Multivariate imaging analysis methods based on machine learning and deep learning will be applied subsequently to investigate relationships between the different modalities and their predictive value for specific symptom dimensions, diagnostic classification and clinical outcomes [30]. Multiple comparisons correction will be applied and will depend on the type of analysis. Missing data will be described and accounted for using a model appropriate for the purpose. For example, using the direct likelihood method and/or multiple imputation [31, 32].

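### Electrode placement in ECT sessions 7 to 10 follows response at session 6, but the stated Objective 3 model adjusts only for age

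*Protocol article*

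**What the plan says.** The Interventions section of the protocol article fixes the starting placement: "Subjects will all be treated with right unilateral (RUL) ECT with stimulus intensity 6 times the initial seizure threshold (ST"). It then makes a change of placement depend on response: "Subjects who failed to respond to RUL ECT after the sixth treatment will be switched to bitemporal ECT (1.5xST").

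The Outcomes section times the imaging as "a baseline measurement prior to ECT and a second measurement after 10 ECT sessions", and gives a reason for the fixed count: "A fixed number of sessions was chosen to reduce bias due to differences in treatment duration".

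For Objective 3, which asks whether hippocampal volume increase after ECT goes with increased synaptic density, the Statistical analysis section says: "we will apply a longitudinal linear mixed model controlling for age, in which hippocampal volume and hippocampal synaptic density are dependent variables". It names no term for electrode placement, number of bitemporal sessions or hemisphere. Table 1 lists only the change in hippocampal volume and the change in UCB-J for this objective.

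The Sample size section powers the ECT arm on a both-sides measure: "we will assess normalized total hippocampal volume on a random sample of patients before and after the last ECT treatment". The Discussion lists medication use and subclinical comorbidity as heterogeneity that cannot be controlled. It does not list placement.

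**The concern.** The fixed session count is meant to make patients comparable at the second scan. It equalises the number of sessions but not what was delivered. By that scan the group contains patients with ten right unilateral sessions and patients with six right unilateral and up to four bitemporal ones. The protocol itself creates this difference, and early response decides who falls on which side of it.

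Objective 3 is a primary objective and concerns an association between two changes. A factor that moves both changes, and is left out of the model, can create such an association or, if it moves them in opposite directions, hide one. Placement is an obvious candidate. It is known for every patient at no extra cost, but the model as written does not use it.

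There is a second consequence. The study also aims to relate imaging biomarkers to therapeutic response to ECT. Where that uses post-ECT imaging change, early response and placement in the last four sessions travel together.

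**Working it through.** **1. Sequence of events**

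| Sessions | Responded by session 6 | Not responded by session 6 |
|---|---|---|
| 1–6 | right unilateral | right unilateral |
| 7–10 | right unilateral | bitemporal (up to 10 − 6 = 4 sessions) |
| Scan after 10 | pooled | pooled |

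Placement in sessions 7–10 is therefore a function of response at session 6.

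**2. The plan's own figure** (Sample size, calculation 2)

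Inputs: mean difference 188.333 mm³ (absolute value), SDs 792.5462 and 864.075 mm³, pre-post correlation 0.92908, n = 20, one-tailed α = 0.05.

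- SD of difference = √(792.5462² + 864.075² − 2 × 0.92908 × 792.5462 × 864.075) = √102,251 = 319.77 mm³
- dz = 188.333 / 319.77 = 0.589
- Paired t-test, noncentral t, n = 20: power 0.814. The stated figure reproduces, so the point is not an arithmetic one.

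**3. How pooling can create an association**

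Assumptions, none of them in the document: a fraction f is switched; switched patients differ by k within-group SDs in both the volume change and the synaptic-density change; within each placement group the two changes are unrelated. The pooled correlation is then

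r = f(1 − f)k² / (1 + f(1 − f)k²).

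For f = 0.3 and k = 1: 0.21 / 1.21 = 0.174. For f = 0.5 and k = 1: 0.25 / 1.25 = 0.20.

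The table shows simulated one-sided rejection rates at n = 20, nominal 5%, for a simple correlation of the two changes (a simplification of the planned mixed model).

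| f | k | Induced r | Pooled | With placement term | Right unilateral only |
|---|---|---|---|---|---|
| 0.3 | 0.5 | 0.05 | about 8% | about 5% | about 5% |
| 0.3 | 1.0 | 0.17 | about 19% | about 5% | about 5% |
| 0.5 | 0.5 | 0.06 | about 8% | about 5% | about 5% |
| 0.5 | 1.0 | 0.20 | about 22% | about 5% | about 5% |

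With k = 0 the induced r is zero and pooling does no harm.

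**4. Precision of the restricted analysis**

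Same dz of 0.589, one-tailed 5%, paired volume test, under assumed switch rates:

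| Switched | n remaining | Power |
|---|---|---|
| 0% | 20 | 0.81 |
| 20% | 16 | 0.73 |
| 30% | 14 | 0.67 |
| 40% | 12 | 0.61 |
| 50% | 10 | 0.53 |

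**5. Side, as an illustration only**

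Let s be the share of the total change that is right-sided and ρ the left-right correlation of change, with equal SDs on both sides. Then dz(right) = s × 0.589 × √(2(1 + ρ)). With ρ = 0.5 and n = 20:

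- s = 0.5: dz 0.51, power 0.71 (0.66 to 0.76 for ρ from 0.3 to 0.7)
- s = 0.75: dz 0.77, power 0.95
- s = 1: dz 1.02, power above 0.99

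The document gives neither s nor ρ. These figures concern mean volume change and do not measure the placement problem. They show why volumes by side are worth reporting, and why total volume should stay primary: under symmetry the right side alone does worse.

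**The case against.** **Much of this could sit in the analysis plan.** A condensed article commonly leaves covariates and sensitivity analyses to a plan that is not shown, and the section says other conventional tests will be applied as well. This lowers the weight of the point. It does not remove it, because the article itself specifies the model for a primary objective and names its covariate.

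**Placement may not be a confounder of Objective 3.** If extra stimulation raises synaptic density and volume follows, placement adds useful variation in exposure and no bias. That is a fair reading, and the illustration above assumes the opposite. The document does not settle it, which is a reason to show results both ways.

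**The remedy cannot separate placement from response.** This stands. Restricting to right unilateral patients selects session-6 responders, and a placement term carries early response with it. Both still help with Objective 3, where response is not a variable.

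**Stronger readings that a reader might infer, and that the text does not support:**

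- *Side is confounded with placement and response.* Side is at most collapsed. The word total, for the ECT arm, occurs only in the sample-size calculation. The outcome, Table 1 and the model say hippocampal volume, and the planned voxel-wise and atlas-based analyses could show side.
- *Placement is fully confounded with clinical response.* The switch depends on response at session 6, and switched patients may still respond by session 10.
- *Every link between imaging and response is affected.* The aim speaks of biomarkers, not of change. Baseline biomarkers precede the switch.

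**Conclusion.** The point holds in limited form. The plan makes stimulation in sessions 7–10 follow session-6 response, and the stated Objective 3 model leaves placement out. A placement-related shift in both measures could then appear as an association between them.

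The size cannot be derived from the document. The 8% to 22% range rests on assumed switch rates of 30% or 50%, assumed shifts of 0.5 to 1 SD in both measures, no within-group association, and a simple correlation in place of the mixed model. Smaller shifts, or a shift in only one measure, would do less or no harm. This is a worthwhile refinement and does not show that Objective 3 fails.

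It also assumes that patients reach ten sessions. The Interventions section treats until remission, the Outcomes section scans after ten sessions, and the Sample size section refers to the last treatment. These passages need to be reconciled.

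**What to change.** The change concerns the analysis only; the switching rule is not in question.

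1. Keep the planned volume measure as primary.
2. Fit volume and UCB-J by hemisphere, with side as a within-patient factor.
3. Report the number of patients switched and the bitemporal sessions each received before the second scan.
4. Add two sensitivity analyses of Objective 3: one with a term for placement or for the number of bitemporal sessions, and one restricted to patients still on right unilateral ECT at the scan.
5. State that these analyses cannot separate placement from early response, so that any relation between post-ECT imaging change and clinical response is read with that limit.

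The cost is two or three extra model runs and segmentation output by side, with no new data collection. The restricted analysis will be imprecise, as the power figures above show, and should be labelled a sensitivity check.
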